### Social Cognition Treatment

Social cognitive training sessions will involve targeting performance in domains of facial affect recognition, prosody detection, body language, and interpersonal communication. Taken together, it is intended that social cognitive treatment will improve subjects’ ability to synthesize a broad spectrum of social information, make clearer theory of mind judgments, and reduce social tension and avoidance. The researcher will emphasize the importance of social cognition in everyday life and encourage participants to exercise acquired social skills outside of treatment sessions. Social cognition training tasks will include a “reading the mind in the eyes” task (77), an interpersonal word list task (78) and theory of mind scenarios (44, 45). These tasks are designed to improve the evaluation of facial affect, verbal tone, and body language, while also highlighting the pitfalls of making unfounded or overly negative assumptions about others’ intentions and emotions.

## Intervention Outcomes, Analyses, and Dissemination

The primary outcome of the CERT-D will be psychosocial functioning. Specifically, it is expected that psychosocial functioning will improve at 8 weeks (end of RCT) relative to baseline. Post-RCT psychosocial functioning is expected to be maintained over the 6 months observational period. Performance in secondary outcome measures is expected to demonstrate a similar effect of treatment. Secondary outcomes include depression symptom severity, occupational functioning, resilience, functional disability, and perceived cognitive failures. In addition, the personalized treatment group is expected to show greater improvement over time relative to the standard treatment group. Finally, the association between biomarkers and psychosocial and cognitive performance before and following treatment will be evaluated.

Statistical analyses will be performed with a mixed model ANOVA with time (baseline, 8 weeks, baseline post-RCT, 3 months post-RCT, 6 months post-RCT) and treatment type (personalized, standard) as independent variables. Psychosocial functioning (FAST score) will be the dependent variable. It is expected that overall psychosocial functioning will improve at post-treatment relative to baseline, and that this improvement will be greater in the personalized treatment arm relative to the standard treatment arm. Biomarker analyses require specifically tailored software and will ultimately be entered into simple and stepwise linear regression analyses. These analyses will determine whether individual biomarkers (e.g., CRP), or combinations of biomarkers, are related to cognition (i.e., THINC-it performance) or psychosocial functioning.

Within the personalized treatment group, further analyses will evaluate whether there are any differences in psychosocial functioning owing to the domain-specific treatment groups. That is, will there be any differences in post-RCT psychosocial functioning between the high cognition, high emotion, and high social cognition treatment groups? Given the novelty of the current treatments, these analyses will be exploratory. As with the primary outcome, analyses for this outcome will be conducted with mixed model ANOVAs.

The anonymized data obtained in the current study will be owned by the University of Adelaide, with access restricted to the research team responsible for the project. The results of the CERT-D study will be published in scientific journals, which will discuss clinical efficacy of personalized and standard approaches in light of the data obtained. The authors will also conduct a public lecture to discuss the broader topic of personalized psychiatry, which will include dissemination of outcomes in the current study.

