**Methods:**

The study is a randomized, controlled treatment (RCT), in which the efficacy of a personalized and standard intervention will be compared. Sixteen treatment sessions will be administered over an 8-week period. These treatments are designed to improve cognition, emotion processing and social cognition. Assessments of psychosocial functioning, as well as a number of secondary outcomes, will occur at baseline, 4 weeks (mid-RCT), 8 weeks (end of RCT), and in the observational period at baseline (week 9) and 3 and 6 months post-RCT. Recruitment will commence in July 2017, including subjects diagnosed with major depressive disorder according to DSM-IV-TR criteria.

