## Methods

### Objectives

The primary objective of the CERT-D is to evaluate whether treating cognition, emotion processing, and social cognition leads to immediate and longitudinal benefit in psychosocial functioning. To achieve this objective, participants will complete either a personalized or standard (non-personalized) treatment devoted to increasing performance in these domains. Participants in the personalized group will receive a tailored treatment incorporating a greater number of sessions devoted to their domain(s) of primary baseline dysfunction. By contrast, the standard treatment group will complete a pre-established battery of treatment independent of baseline deficits.

The key hypotheses and aims of the current study are as follows:
*Hypothesis 1*:Overall, psychosocial functioning will be improved at 8 weeks [end of randomized, controlled treatment (RCT)] relative to baseline. Psychosocial functioning in the observational period (post-RCT) will not decline at 3 and 6 months relative to post-RCT baseline.*Related Aim*:To evaluate which subdomains of psychosocial function (e.g., autonomy, social relationships) are sensitive to change over time from the CERT-D.*Hypothesis 2*:Performance in secondary outcome measures will improve at 8 weeks relative to baseline, and will be retained over a 6-month observational period. Secondary outcomes include occupational functioning, cognitive failures, functional disability, resilience, and depression symptom severity.*Hypothesis 3*:It is expected that the personalized treatment group will display greater psychosocial improvement at 8 weeks (compared to baseline) than subjects who complete a standard treatment.*Hypothesis 4*:Biological and genomic signatures will be associated with psychosocial functioning, as well as cognitive, emotional, and social cognitive performance.

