### Study Design and Recruitment

The CERT-D study will commence in July 2017. The study will be a RCT, comparing the clinical efficacy of a personalized and standard intervention. Psychosocial functioning is considered the primary outcome. An effect size of approximately *d* = 0.5 is expected with regards to change in psychosocial function over the intervention. Given the intended sample size of 100, the study will achieve statistical power of 89% (1 − β = 89). The rationale for this “medium” effect size is that previous interventions have found positive outcomes approximate to this magnitude (5, 35), for example in cognitive functioning.

The trial will include 16 treatment sessions designed to improve cognition, emotion processing, and social cognition administered over an 8-week period. Assessments will occur at baseline, 4 weeks (mid-RCT), 8 weeks (end of RCT), and in the observational period at baseline (week 9) and 3 and 6 months post-RCT (see Figure 1). Assessments will measure psychosocial functioning, cognition, emotional state, social cognition, as well as occupational functioning, depression symptom severity, functional disability, cognitive failures, and resilience. Three assessment visits will also include taking blood for biomarker and genetic analysis. Recruitment will include individuals between the ages of 18 and 75, who will be invited to participate *via* research clinics of the Department of Psychiatry, University of Adelaide, and within the Central Health Network in Adelaide, South Australia. It could be argued that the age range should be restricted to younger adults (<60), such that subjects with geriatric depression are excluded. However, recent work has suggested that cognitive training strategies are efficacious in the treatment of geriatric depression (47, 51, 52). Given the current intervention shares many components of traditional cognitive training, it is suggested that the CERT-D intervention should benefit older (i.e., 60–75 years) patients.

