### Inclusion and Exclusion Criteria

Individuals with mild–moderate MDD according to DSM-IV-TR criteria (17) will be recruited for the current study. Severely depressed subjects will not be included, as the complexity from treatment tasks would likely result high rates of deterrence. Subjects identified through screening with bipolar or anxiety disorders will be excluded, as will subjects with schizophrenia, a learning disorder, eating disorder or a pervasive developmental disorder. Subjects with current brain injury or impairment which could affect cognitive function (e.g., neurodevelopmental disorders, dementia) will be excluded. In addition, subjects will be withdrawn following subsequent severe brain/head injury, development of dementia, psychosis, or development of neurological conditions such as multiple sclerosis or Parkinson’s disease.

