### Ethics

The CERT-D has been approved by the Human Research Ethics Committees at the Royal Adelaide Hospital (approval number: R20170611) and The University of Adelaide (approval number: R20170611). All details of participant involvement will be conveyed to study participants both in writing and verbally before informed consent is obtained.

There are no severe adverse effects expected to result from the current treatment. However, participants will be withdrawn from treatment if they demonstrate a significant increase in depression symptom severity [20% increase in Montgomery Asberg Depression Rating Scale (MADRS) score] and referred to their treating psychiatrist or GP.

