### Assessment Visits (Baseline—6 Months Post-RCT)

In total, six assessments of functioning and performance will occur over the CERT-D timeline (see Figure 1). In the intervention period, subjects will complete assessments at baseline, 4 weeks (mid-RCT), and 8 weeks (end of RCT). The observational period will comprise assessments in week 9 (baseline post-RCT), as well as 3 and 6 months post-RCT.

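### The five-level FAST model leaves out the scheduled week-4 score, which would partly protect the week-8 change if participants who worsen early are later lost to assessment

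*Protocol article*

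**What the plan says.** **Visits.** The abstract's Methods paragraph schedules FAST's construct during treatment: "Assessments of psychosocial functioning, as well as a number of secondary outcomes, will occur at baseline, 4 weeks (mid-RCT), 8 weeks (end of RCT". Study Design and Recruitment repeats it: "Assessments will measure psychosocial functioning, cognition, emotional state, social cognition", among other measures. The section on assessment visits gives the count: "In total, six assessments of functioning and performance will occur over the CERT-D timeline". The six are baseline, week 4, week 8, week 9, 3 months and 6 months.

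**Model.** Intervention Outcomes, Analyses, and Dissemination gives a "mixed model ANOVA with time (baseline, 8 weeks, baseline post-RCT, 3 months post-RCT, 6 months post-RCT", crossed with treatment type. "Psychosocial functioning (FAST score) will be the dependent variable". Week 4 is not among the levels. No reason is given, and no other use of the week-4 FAST is described.

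**Hypothesis.** Under Objectives, Hypothesis 1 is that "psychosocial functioning will be improved at 8 weeks" relative to baseline, overall. It is not a comparison between arms. Hypothesis 3 is the comparison between arms.

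**Stopping treatment.** Under Ethics, "participants will be withdrawn from treatment if they demonstrate a significant increase in depression symptom severity", set at a 20% rise in MADRS. The article does not say whether such participants go on attending assessments.

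**The concern.** Week 4 is the only scheduled FAST between baseline and the end of training. For a participant who deteriorates early and then misses every later visit, it is the only post-baseline record of the primary outcome. A model with the five stated levels does not draw on it. If incomplete participants are dropped, this person disappears. If the five levels are fitted by likelihood, only the baseline remains, and the model in effect predicts week 8 from people who stayed.

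Hypothesis 1 has no untreated comparator to cancel such selection. If those lost are on average those who worsened, the estimated change moves toward the hoped-for improvement.

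**Working it through.** **1. Visits against model.** Six FAST assessments are scheduled and five enter the model, so one is left out: week 4.

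**2. The plan's power figure.** The article gives 89% power for n = 100 and d = 0.5. It reproduces as a repeated-measures between-group F test with f = d/2 = 0.25, taking correlation ρ = 0.5 and α = 0.05 (neither is stated):

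- λ = N f² m / (1 + (m − 1)ρ)
- m = 5: 100 × 0.0625 × 5 / 3 = 10.4, power 0.892
- m = 6: 100 × 0.0625 × 6 / 3.5 = 10.7, power 0.900

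Power is therefore not the reason to add week 4.

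**3. Illustrative bias in the week-8 change.** From the article: n = 100 and the 20% MADRS rule. All else is assumed:

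- Baseline MADRS mean 20, SD 5, limited to 10–34. A participant is withdrawn if the MADRS change by week 4 is at least 0.2 × baseline.
- FAST SD 1 and no true FAST change. Correlation of baseline with week 4 is 0.6 and with week 8 is 0.5, so the week-8 change also has SD 1. The week-4 and week-8 changes correlate 0.7.
- MADRS change correlates r with the week-4 FAST change and 0.8r with the week-8 change. Baseline MADRS and FAST correlate 0.4.
- Settings (mean and SD of MADRS change; r; withdrawn): A: −4, 5; 0.3; 5.8%. B: −2, 6; 0.5; 16.2%. C: 0, 8; 0.5; 30.8%.

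Spurious improvement in SD, with the rate of significant false improvement in brackets (nominal 2.5%), 4000 runs per setting:

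| Setting | Reassessed at week 8 | Listwise, 5 levels | Likelihood, 5 levels | Likelihood, 6 levels |
|---|---|---|---|---|
| A | none | 0.032 (5.0%) | 0.027 (4.5%) | 0.006 (2.9%) |
| A | half | 0.018 (3.4%) | 0.016 (3.1%) | 0.005 (2.6%) |
| B | none | 0.125 (21.3%) | 0.116 (18.8%) | 0.033 (4.9%) |
| B | half | 0.055 (8.2%) | 0.051 (7.1%) | 0.012 (3.4%) |
| C | none | 0.215 (46.0%) | 0.203 (44.8%) | 0.063 (7.9%) |
| C | half | 0.087 (12.2%) | 0.082 (10.8%) | 0.021 (3.6%) |

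With all reassessed, bias is within 0.002 in every model. A six-level listwise ANOVA equals the five-level one throughout. A large-sample repeat agreed within about 0.003; its lowest five-level value with half reassessed was 0.014, hence the lower end of 0.01.

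**4. Hand check of the listwise column.** If a fraction q is lost, bias = q/(1 − q) × (mean week-8 change of the lost minus that of everyone). For C with none reassessed, the implied excess is 0.215 × 0.692/0.308 = 0.483 SD. With half lost, q = 0.154 and the formula gives 0.154/0.846 × 0.483 = 0.088, against 0.087 simulated.

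**5. A different loss model.** Here week 8 is missed depending on week-4 FAST worsening itself, with 8% to 32% of an arm missing. A five-level likelihood fit overstates improvement by 0.03 to 0.13 SD, and week 4 brings it within 0.002 of the truth. That near-complete recovery follows from letting loss depend on the very score added. The MADRS-driven model in step 3 is the more cautious guide.

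**6. Limit of the remedy.** If a quarter of those lost leave before week 4 and none are reassessed, the six-level likelihood model leaves 0.011, 0.052 and 0.089 SD in A, B and C.

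**The case against.** **This is missing-data handling, which belongs in the SAP.** Partly right. Silence on estimation and analysis sets is no fault in a condensed article. But the article does state the list of time levels, and that list leaves out a scheduled measurement of the primary outcome.

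**Five levels match the hypotheses.** They do, and the tested contrasts need no change. Nor is the week-4 score strictly unusable: it could serve as an auxiliary variable in multiple imputation or in a sensitivity analysis, neither of which the article rules out. The fair statement is that the stated model does not use it.

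**The loss is not in the document.** A reader might infer from the MADRS rule that worsening participants leave the study. The text withdraws them from treatment, not from assessment, and with full reassessment there is no bias. A reader might also take "Severely depressed subjects will not be included, as the complexity from treatment tasks would likely result high rates of deterrence" as a forecast of dropout. It concerns people who are not enrolled and cites task complexity, so it is no evidence of selective loss among the mild to moderate participants who are.

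**The figures are assumed, and some participants return.** Both stand. The simulation models only baseline, week 4 and week 8. Someone who misses week 8 but attends week 9 or later contributes post-baseline FAST to the five-level likelihood model, so the rows with none reassessed overstate its bias for such participants.

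**Adding week 4 to an ordinary ANOVA changes nothing.** Correct if that ANOVA drops incomplete participants, which the article does not settle. The fitting method is therefore part of the remedy.

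**Conclusion.** The point holds as an improvement to robustness. The article schedules a week-4 FAST and states a primary model that does not use it, while Hypothesis 1 rests on an uncontrolled change. If participants who worsen by week 4 are lost afterwards, improvement may be overstated: about 0 SD if all are reassessed, 0.01 to 0.09 SD if half are, and 0.03 to 0.2 SD if none are and none return. These ranges rest on assumed withdrawal rates of 6% to 31% and assumed correlations. They illustrate the mechanism and do not predict this trial's bias.

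A reader might extend the point to Hypothesis 3. The documents do not support that: nothing indicates unequal loss between arms, and in the alternative loss model the arm difference moved only from −0.50 to between −0.496 and −0.471. Confidence is medium, because the loss is plausible but not stated.

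**What to change.** In Intervention Outcomes, Analyses, and Dissemination, replace the five-level mixed model ANOVA with a likelihood-based linear mixed model for FAST with six time levels: baseline, weeks 4, 8 and 9, and 3 and 6 months. Include every randomised participant with any FAST score, in the arm to which they were randomised. Keep the contrasts: week 8 against baseline for Hypothesis 1, and the difference in that change between arms for Hypothesis 3.

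Make both changes together. In setting C with none reassessed, likelihood fitting alone moves the bias from 0.215 to 0.203 SD, and week 4 in a listwise ANOVA leaves it at 0.215. The two together bring it to 0.063.

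The cost is one more time level and slightly more modelling work, with no new visit or procedure. The protection is partial and does nothing for participants lost before week 4. As an optional clarification, say that FAST visits continue after withdrawal from treatment; full reassessment would remove this source of bias.

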### Cognitive Impairment

According to DSM-5 criteria the cognitive symptoms of major depressive disorder (MDD) are impaired decision making, management of attention, and coordination and maintenance of information in working memory (17). Research has also identified deficits in verbal ability (18), visuospatial processing (19), and psychomotor speed (19). The finding that cognitive deficits occur across multiple domains suggests that depression interferes with underlying cognitive faculties, and with the coordination of cognitive subsystems, rather than interfering a specific modality of cognition. Our cognitive abilities are crucial to daily functioning, and to the severity of several cognitive difficulties associated with depression (e.g., hyper-sensitivity to negative feedback). Cognitive treatments target improvement of cold cognition, with the rationale that increasing functioning will benefit performance in hot cognitive tasks, and hence improve experience of everyday life, psychosocial functioning, and day-to-day functioning. In addition, cognitive impairments may mutually interact with emotional and social factors to maintain or exacerbate depression, or lead to recurrent episodes (14, 16).

Psychosocial and cognitive impairments in depression and in other illnesses are associated with elevated levels of several inflammatory cytokines (20, 21). Research by the [name] group (22, 23) demonstrated that IL-8, IL-1beta, and tumor necrosis factor (TNF) are associated with memory, processing speed and motor function in the elderly. In addition, inflammatory C-reactive protein (CRP) may also be associated with depression symptoms (24), and the neurotransmitters 5HT, DA, and NE appear to be related to psychological stress (25). Investigating biomarkers for psychosocial functioning and cognitive dysfunction presents a valuable area for research, as there is potential for developing objective measurements of dysfunction predisposition, for improving our understanding of the neurological mechanisms of depression and associated poor psychosocial functioning (e.g., neurotrophic theory), and for improving pharmacological treatments that address not only symptoms of depression but also psychosocial functioning and workplace functioning.

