#### Cognitive Functioning

Cognitive functioning will be assessed with the THINC-it tool; a digitally administered screening instrument for cognitive impairment in depression. The THINC-it involves four objective tests of cognitive performance, including choice reaction time, a *1*-back memory task, the Trail Making Test Part B and digit symbol substitution. The THINC-it also includes a 5-item component of the self-reported perceived deficit questionnaire, as an indication of retrospective cognitive dysfunction (56).

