#### Blood Specimen

Blood taking will occur at baseline, week 8 (end of RCT), and at 6 months post-RCT. These samples will enable analyses of biomarker associations with psychosocial functioning, as well as the effect of the CERT-D intervention on biomarker levels. Blood serum analyses will include of evaluation of cytokine concentration (e.g., IL-8, TNF), CRP levels, and neurotransmitter activity. Samples will be stored in secure refrigerators with stringent access rights at the Adelaide Health and Medical Sciences building.

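### As described, the biomarker regressions cannot separate a marker's association with cognition or psychosocial functioning from age, in a sample aged 18 to 75

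*Protocol article*

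**What the plan says.** Hypothesis 4, in the Objectives section, reads: "Biological and genomic signatures will be associated with psychosocial functioning, as well as cognitive, emotional, and social cognitive performance". The Blood Specimen section names the markers: "Blood serum analyses will include of evaluation of cytokine concentration (e.g., IL-8, TNF), CRP levels, and neurotransmitter activity".

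The section on Intervention Outcomes, Analyses, and Dissemination gives the method. The biomarker data "will ultimately be entered into simple and stepwise linear regression analyses", and these are to determine "whether individual biomarkers (e.g., CRP), or combinations of biomarkers, are related to cognition (i.e., THINC-it performance) or psychosocial functioning". The text does not label outcome and predictor, but the reference to combinations of biomarkers implies that the markers are the predictors.

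Cognition is measured as described under Cognitive Functioning: "The THINC-it involves four objective tests of cognitive performance" (choice reaction time, 1-back, Trail Making Test Part B, digit symbol substitution), plus a short self-report part. That section does not say whether scores are age-standardised. Study Design and Recruitment admits "individuals between the ages of 18 and 75" and gives an intended sample of 100. No covariate is named for the biomarker regressions.

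**The concern.** Age is a plausible common cause of a marker level and a cognition score. If both drift with age, a regression of one on the other shows a slope even when the marker has no link to cognition beyond age. The range here is wide (75 − 18 = 57 years), and the section on study design deliberately keeps patients over 60. Its argument for doing so is that older patients should also benefit from the training. That supports eligibility and does not bear on confounding in the biomarker models.

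Hypothesis 4 is at stake. It is one of four key hypotheses, and the Discussion counts the biological correlates among the study's three main contributions. The Introduction hopes for objective measures of a predisposition to dysfunction, and a marker that only stands in for age would not provide one.

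**Working it through.** **What the article fixes.** A simple linear regression has a single predictor. If that predictor is the marker, age is outside the model by definition, and a later analysis plan could not add age and still call the regression simple. For the stepwise models the only terms described are combinations of biomarkers. The list is not stated to be closed. But even if age were a candidate, stepwise selection could drop it unless it is forced in.

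**Size.** The article states no figure for these regressions, so there is none to reproduce.

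Inputs:
- n = 100, the intended sample size (Study Design and Recruitment).
- Two-sided test at 0.05 for each marker: assumption.
- a = |r(age, marker)| and c = |r(age, cognition score)|: assumptions, varied below. The article gives neither.
- No association between marker and cognition once age is held fixed, so that every rejection is a false positive.

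Formulas:
- Correlation induced by age alone: r = a × c.
- Rejection rate of the unadjusted regression, by Fisher's z: m = artanh(r) × √(n − 3), then P(Z > 1.96 − m) + P(Z < −1.96 − m).

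Worked case, a = 0.3 and c = 0.5: r = 0.15, artanh(0.15) = 0.1511, √97 = 9.849, m = 1.489. The rate is P(Z > 0.471) + P(Z < −3.449) = 0.319.

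A simulation of 20,000 data sets per scenario (normal variables) gave the rates without and with age in the model:

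| a | c | induced r | Fisher z | simulated, no age | simulated, age in model |
|---|---|---|---|---|---|
| 0 | 0.5 | 0 | 5.0% | 4.8% | 4.8% |
| 0.1 | 0.3 | 0.03 | 6.0% | 6.2% | 5.1% |
| 0.2 | 0.4 | 0.08 | 12.4% | 12.4% | 4.9% |
| 0.3 | 0.4 | 0.12 | 22.1% | 22.2% | 5.0% |
| 0.3 | 0.5 | 0.15 | 31.9% | 32.6% | 5.0% |

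The two methods agree. The inflation runs from nothing to about sixfold over this range, and including age removes it in every row. If fewer than 100 participants give usable blood samples, √(n − 3) falls, and the inflation at the same correlations is smaller.

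For models with psychosocial functioning as outcome the same formula applies, with the age–FAST correlation in place of c. No value for it was assumed, so no size is claimed there.

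**The case against.** The strongest reply is that this is a condensed article that gives the biomarker analysis two sentences, and that covariate lists normally belong in the analysis plan. That reply holds for the stepwise models: their candidate terms are not listed, and nothing says that age is kept out. It does not hold for the simple regressions, because naming that model is itself the choice that leaves age out.

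A second reply is that the size rests wholly on assumed correlations. This stands. If THINC-it scores are fully age-normed, or a marker does not vary with age, the bias is zero. The article's own supporting evidence does not settle the matter. It says that certain cytokines "are associated with memory, processing speed and motor function in the elderly", which is an association within an older group and says nothing about how markers or scores change between 18 and 75.

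A third reply is that Hypothesis 4 speaks only of association, for which a crude correlation is a fair first description. That is reasonable for a descriptive result. But the article says that these regressions will determine relatedness, and its exploratory label is attached to the comparison of the personalised streams, not to the biomarker work.

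Two stronger readings are tempting and should not be made:
- **That the regressions will report age differences as biomarker findings.** The documents support only that they cannot separate the two.
- **That the missing age term also undermines the randomised FAST comparison.** Allocation is random, so chance age imbalance is already covered by the nominal error rate. Hypothesis 3 also concerns change from baseline, so a stable age difference in FAST level drops out of the time-by-treatment contrast. Age adjustment there is an optional gain in precision.

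**Conclusion.** The point holds for the biomarker regressions and only for them. The simple regressions leave age out by construction, and the stepwise models give no assurance that it is in. A significant marker could therefore reflect age alone. At n = 100 the false-positive rate per marker lies between 5% (no age link) and about 32% (age correlations of 0.3 and 0.5), with 6% and 12% for the weaker cases of 0.1 with 0.3 and 0.2 with 0.4. These figures assume a two-sided 0.05 test, no true marker effect given age, and correlations that the article does not supply. Hypothesis 4 is affected; the primary outcome is not.

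**What to change.** - Force age and sex into every biomarker regression, simple or stepwise, before any marker is tested or selected, and keep them in regardless of significance.
- Base the conclusions for Hypothesis 4 on the adjusted associations.
- Report the unadjusted simple regressions as descriptive only.
- State whether THINC-it scores are age-standardised. Full standardisation would remove the problem for the cognition models, but not for those with psychosocial functioning as outcome.

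The cost is a few lines of wording and one or two degrees of freedom per model out of about 100 observations. Age must be known to apply the eligibility limits. Sex is presumably recorded too, although the article does not say so.
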